**Results:**

Ten participants with MS and eight healthy controls were recruited between October 2008 and March 2009. Mesenchymal stem cells were successfully isolated, expanded and characterised *in vitro *for all participants in the treatment arm.

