Functional MR imaging was performed by acquiring T2* -weighted images depicting blood oxygen level dependent (BOLD) contrast: near axial (whole brain), TR = 3940 ms, TE = 30 ms, matrix size = 64 × 64, FOV = 192 mm, slice thickness = 3 mm. Four experiments of 5 minutes duration were performed using differing visual stimulation patterns as previously described [22]. Briefly, in a five-minute experiment, the subject uses binocular vision through red-green filter goggles to view a projected monitor while lying in the scanner. A reversing checkerboard pattern was shown for sixteen-second epochs of red or green stimuli, alternating with sixteen-second epochs of no stimulation. Red and green colour patterns were presented randomly in order to avoid predictability. The red-green filters were reversed by swapping the goggles between each five-minute session (*ie*. if the first run had red filter for the right eye, this was changed to green for the second run). Monocular stimulation was achieved for each epoch by matching the colour of stimulus and filter so that the eye looking through the red filter could only see the red checkerboard pattern while the other eye was unstimulated by red (and vice versa for green). Each five-minute experiment consisted of four epochs of green and four of red, thus stimulating both eyes four times each. Attention was monitored by a manual response task in the non-stimulation epochs. Analysis was performed using Statistical Parametric Mapping software (SPM 8.0, Wellcome Trust Centre for Neuroimaging, UCL, London, UK). Images were realigned, co-registered, and normalised to the T1 volumetric image obtained at that session. Images were then smoothed, and the experimental model was specified. Effects were analysed for each eye independently.

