### Blinding and data analysis

Optic nerve area, optic nerve MTR, and optic nerve DTI based outcomes were assessed by observers blind to participant status (pre/post-treatment). Lesional analysis was performed shortly after image acquisition at each visit. Brain volume, brain MTR, and fMRI analyses were performed using automated methods with minimal manual corrections; blinding was not therefore performed. Group comparisons for baseline outcomes were performed by Student's t-test. Following trial completion, safety data will be analysed to assess whether the post-intervention period is associated with an increase in adverse events; and efficacy data will be analysed to assess whether the post-intervention period is associated with a difference in pre-defined outcomes. No interim analyses are planned.

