#### (ii) Optic nerve-based measures

Baseline results for optic nerve-based outcomes are shown in table 4. Visual evoked potentials were abnormal in all treatment arm participants (18 of 20 eyes showing changes consistent with demyelination). Retinal nerve fibre layer thickness was reduced by 15.3% in patients' eyes with a previous history of optic neuritis or Unthoff's phenomenon (clinically affected) compared to clinically unaffected eyes (Absolute values: 72.4 μm [SD 12.9 μm] *vs*. 85.5 μm [SD 10.2 μm]; p = 0.0399). Full-field VER latency was prolonged by 18.7% in clinically affected eyes compared to clinically unaffected eyes (Absolute values: 136.3 ms [SD 15.2 ms] *vs*. 114.8 ms [SD 7.1 ms]; p = 0.0045).

**Table 4 T4:** Optic nerve-based measures in treatment group

	Clinically Affected (mean, SD)	Clinically Unaffected (mean, SD)	p
**Number of optic nerves (n)**	14	6	
			
**LogMAR**	0.15 (0.20)	0.15 (0.17)	0.9640
**Sloan 25%**	0.31 (0.26)	0.30 (0.20)	0.9746
**Sloan 5%**	0.66 (0.35)	0.53 (0.18)	0.4282
**Sloan 1.25%**	1.0 (0.46)	0.75 (0.15)	0.1544
			
**FM-100 Square-Root Total Error Score**	16.0 (4.4)	13.5 (2.8)	0.2188
**Visual field Mean Deviance**	-4.28 (2.04)	-3.04 (2.06)	0.2267
			
**RNFL average thickness (microns)**	72.4 (12.9)	85.5 (10.2)	0.0399
**Macular volume (mm^3^)**	6.1 (0.5)	6.6 (0.3)	0.0624
			
**Full field VER latency (milliseconds)**	136.3 (15.2)	114.8 (7.1)	0.0045
**Full-field VER amplitude (microvolts)**	4.8 (1.9)	4.5 (2.3)	0.7669
			
**Optic nerve area (mm^2^)**	8.1 (1.3)	8.9 (1.1)	0.1961
**Optic nerve MTR (pu)**	28.4 (2.9)	31.3 (2.3)	0.0515
			
**Optic nerve DTI Mean Diffusivity (×10^-3 ^mm^2^/s)**	1.17 (0.29)	1.25 (0.26)	0.5415
**Optic nerve DTI Fractional Anisotropy (×10^3^)**	298.2 (91.2)	353.3 (88.6)	0.2282
**Optic nerve DTI Radial Diffusivity (×10^-3 ^mm^2^/s)**	0.99 (0.26)	1.03 (0.24)	0.7004
**Optic nerve DTI Axial Diffusivity (×10^-3 ^mm^2^/s)**	1.53 (0.42)	1.70 (0.35)	0.4012
			

FM-100 = Farnsworth-Munsell 100-Hue test; RNFL = Retinal Nerve Fibre Layer; VER = Visual Evoked Response; DTI = Diffusion Tensor Imaging.

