#### (iii) Comparative performance between patients and controls

Normalised brain volume was reduced by 11.1% in patients compared to controls (Absolute values: 1486 cm^3 ^[SD 75 cm^3^] *vs*. 1671 cm^3 ^[SD 53 cm^3^]; p < 0.00005). There were no significant differences in brain imaging MTR measures between controls and patients although there was a trend to higher MTR values in controls. Whole brain (mean) MTR was reduced by 5.3% in patients (Absolute values: 44.52 pu [SD 6.56 pu] *vs*. 47.02 pu [SD 4.48 pu]; p = 0.3976). Grey matter (mean) MTR was reduced by 7.2% in patients (Absolute values: 35.20 pu [SD 7.34 pu] *vs*. 37.95 pu [SD 5.14 pu]; p = 0.4061). White matter (mean) MTR was reduced by 4.6% in patients (Absolute values: 46.37 pu [SD 6.92 pu] *vs*. 48.63 pu [SD 4.49 pu]; p = 0.4623).

Optic nerve-based measures showed significant differences between patients and controls in measures of RNFL average thickness and optic nerve area, and in DTI measures of mean diffusivity, fractional anisotropy and radial diffusivity (table 5).

**Table 5 T5:** Optic nerve-based measures in patients and controls

	PATIENTS		CONTROLS	
			
	Clinically Affected (mean, SD)	Clinically Unaffected (mean, SD)	(mean, SD)	p*
**Number of optic nerves (n)**	14	6	16	-
				
**RNFL average thickness (microns)**	72.4 (12.9)	85.5 (10.2)	101.6 (12.1)	0.0093
**Macular volume (mm^3^)**	6.1 (0.5)	6.6 (0.3)	6.9 (0.4)	0.1211
				
**Optic nerve area (mm^2^)**	8.1 (1.3)	8.9 (1.1)	10.3 (0.8)	0.0123
**Optic nerve MTR (pu)**	28.4 (2.9)	31.3 (2.3)	32.9 (3.4)	0.2700
				
**Optic nerve DTI Mean Diffusivity (×10^-3 ^mm^2^/s)**	1.17 (0.29)	1.25 (0.26)	0.97 (0.13)	0.0145
**Optic nerve DTI Fractional Anisotropy (×10^3^)**	298.2 (91.2)	353.3 (88.6)	530.6 (99.7)	0.0004
**Optic nerve DTI Radial Diffusivity (×10^-3 ^mm^2^/s)**	0.99 (0.26)	1.03 (0.24)	0.67 (0.13)	0.0007
**Optic nerve DTI Axial Diffusivity (×10^-3 ^mm^2^/s)**	1.53 (0.42)	1.70 (0.35)	1.58 (0.23)	0.4809
				

RNFL = Retinal Nerve Fibre Layer; VER = Visual Evoked Response; DTI = Diffusion Tensor Imaging. * Significance test for control *vs*. patient by 2-way ANOVA controlling for optic nerve status in patient group (clinically affected/unaffected)

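### Tables 4 and 5 test eyes as if they were independent, although 36 eyes come from 18 people, so their baseline standard errors and p-values are wrong

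*Protocol article*

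**What the plan says.** The Abstract gives the number of people: "Ten participants with MS and eight healthy controls were recruited". In the Methods, under Blinding and data analysis, the one test named for baseline data is in the sentence "Group comparisons for baseline outcomes were performed by Student's t-test".

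Table 4 (Results, Optic nerve-based measures) compares 14 clinically affected with 6 clinically unaffected optic nerves. These are both eyes of every patient, as the text confirms: "18 of 20 eyes showing changes consistent with demyelination". The section highlights two results, RNFL ("72.4 μm [SD 12.9 μm] *vs*. 85.5 μm [SD 10.2 μm]; p = 0.0399") and full-field VER latency ("136.3 ms [SD 15.2 ms] *vs*. 114.8 ms [SD 7.1 ms]; p = 0.0045").

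Table 5 sets the same 14 and 6 patient eyes against 16 control eyes. Its footnote describes the test: "Significance test for control *vs*. patient by 2-way ANOVA controlling for optic nerve status in patient group (clinically affected/unaffected". The only covariate is eye status. Pairing, a person-level mean, a participant effect or any other allowance for clustering is not mentioned for either table.

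**The concern.** Two eyes of one person tend to resemble each other. An analysis that counts them as separate observations uses the wrong standard error. It is too small when the contrast is between people and too large when the contrast is between the two eyes of the same person. Table 5 contrasts different people. Table 4 may mix both kinds of contrast, so its error can go either way.

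The eye measures carry the article's sentinel lesion method: acuity, contrast, colour, fields, RNFL, macular volume, VER, nerve area, MTR and DTI. The article offers this method as a model for other trials, and these tables are its evidence that the measures separate affected from unaffected eyes and patients from controls. Several of the p-values lie close to 0.05.

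**Working it through.** **Inputs from the article.** 10 patients and 8 controls; 14, 6 and 16 eyes; the means, SDs and p-values of Tables 4 and 5.

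**Assumptions, because the article gives neither.** Inter-eye correlation ρ from 0.3 to 0.9. Number of split patients k, meaning one affected and one unaffected eye. With 14 and 6 eyes in 10 people, k can be 0, 2, 4 or 6; then a = (14 − k)/2 patients have both eyes affected and b = (6 − k)/2 have both unaffected.

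**Step 1: reproduce Table 4.** Unpaired equal-variance t-test on 14 vs 6 eyes, 18 df. For RNFL:
- pooled SD = √[(13 × 12.9² + 5 × 10.2²)/18] = 12.21
- SE = 12.21 × √(1/14 + 1/6) = 12.21 × 0.488 = 5.96
- t = 13.1/5.96 = 2.20, p = 0.041 (printed 0.0399; 0.0391 to 0.0434 allowed by rounding of the inputs)

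The same calculation gives VER latency 0.0042 (printed 0.0045, at the upper edge of what rounding allows), FM-100 0.2187 (printed 0.2188) and fractional anisotropy 0.2280 (printed 0.2282). All 16 p-values agree within rounding, although for coarsely rounded rows such as macular volume that is a weak check.

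**Step 2: reproduce Table 5.** Controls have no affected level, so in a linear model the patient-control effect adjusted for eye status is 16 control eyes vs 6 unaffected patient eyes, with the residual pooled over all 36 eyes (33 df). For RNFL:
- residual SD = √[(13 × 12.9² + 5 × 10.2² + 15 × 12.1²)/33] = 12.16
- t = 16.1/[12.16 × √(1/16 + 1/6)] = 2.77, p = 0.0092 (printed 0.0093)

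Mean diffusivity gives 0.0142 (printed 0.0145) and fractional anisotropy 0.0004 (printed 0.0004). All 8 agree within rounding.

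**Step 3: effect of clustering on the SE**, in units of the eye-level variance.
- Table 4: true variance = (1/14)(1 + 2aρ/14) + (1/6)(1 + 2bρ/6) − 2kρ/84; used = 1/14 + 1/6 = 0.2381
- Table 5: true variance = (1/16)(1 + ρ) + (1/6)(1 + 2bρ/6); used = 1/16 + 1/6 = 0.2292

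Example, Table 4, k = 6 (a = 4, b = 0), ρ = 0.9: 0.1082 + 0.1667 − 0.1286 = 0.1463; ratio √(0.1463/0.2381) = 0.78. With k = 0 both ratios reduce to √(1 + ρ).

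Ratio of true SE to SE used, and simulated type I error of the nominal 5% test (200,000 runs per cell), each for ρ = 0.3 to 0.9:

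| Split patients k | Table 4 SE ratio | Table 4 type I error | Table 5 SE ratio | Table 5 type I error |
|---|---|---|---|---|
| 0 | 1.14–1.38 | 9–18% | 1.14–1.38 | 9–17% |
| 2 | 1.08–1.21 | 7–12% | 1.11–1.30 | 8–15% |
| 4 | 1.01–1.02 | 5–6% | 1.07–1.21 | 7–12% |
| 6 | 0.93–0.78 | 4–1% | 1.04–1.12 | 6–9% |

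**Step 4: what this does to the printed p-values.** Take the t implied by the printed p, divide by the SE ratio and keep the article's df. The two extremes are k = 0 and k = 6, both at ρ = 0.9.

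| Table 4 outcome | Printed p | Implied t | k = 0 (t/1.378) | k = 6 (t/0.784) |
|---|---|---|---|---|
| RNFL | 0.0399 | 2.215 | 0.125 | 0.011 |
| Optic nerve MTR | 0.0515 | 2.086 | 0.148 | 0.016 |
| Macular volume | 0.0624 | 1.987 | 0.167 | 0.021 |
| VER latency | 0.0045 | 3.244 | 0.030 | 0.0006 |

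The pooled SD is itself slightly too small under clustering. Allowing for that, the RNFL range becomes 0.013 to 0.148. VER latency stays below 0.05 with 18 df; with that allowance and about 8 df (10 people, two groups) it reaches 0.054 in the worst case.

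In Table 5 with k = 0, ρ = 0.9 and 33 df, RNFL moves from 0.0093 to 0.053, nerve area from 0.0123 to 0.063 and mean diffusivity from 0.0145 to 0.070. Fractional anisotropy (0.007) and radial diffusivity (0.011) stay well below 0.05. With k = 6, ρ = 0.9 and 16 df (18 people, two groups), all five significant results stay below 0.05; the largest is 0.034.

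**The case against.** The strongest reply concerns scope and direction, since the eye counts and the reproduced p-values are not in doubt.

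- **Direction in Table 4.** A reader might infer that every patient has at least one affected eye, so that six patients are split and the printed standard errors are simply too large (by 13% at ρ = 0.5 and 28% at ρ = 0.9). The article does not establish this. The footnote to its eligibility table also accepts optic atrophy on examination, whereas an affected eye in the baseline results is defined by optic neuritis or Uhthoff's phenomenon alone. All four pairings remain open. With none or two split patients the direction reverses, and with four the effect is negligible. This objection stands.
- **Size in Table 5.** A reader might quote a type I error of 8 to 17%, which belongs to a plain comparison of 20 with 16 eyes. The ANOVA in the footnote is a different contrast. With six split patients its error is about 6 to 9%, and no Table 5 conclusion changes. This stands too, although the standard error is still too small under every pairing.
- **Efficacy analysis.** A reader might infer that the pre/post analysis will have inflated false positives. The article states neither unit nor model for it, and the correlation that would matter there is that between the two eyes' changes. No error is shown.
- **fMRI.** The sentence "Effects were analysed for each eye independently" closes a description of monocular stimulation and image modelling. It means that each eye's response is estimated separately, not that eyes are independent sampling units, and it gives no support here.
- **Importance.** These are baseline tables in a phase IIA study whose primary objective is safety, and the brain measures, which are per person, are unaffected. That limits the consequence but does not make the p-values right.

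**Conclusion.** The point holds for the baseline eye-level comparisons in Tables 4 and 5. They treat 20 patient eyes and 16 control eyes as independent although they come from 10 patients and 8 controls. In Table 4 the true standard error is 0.78 to 1.38 times the one used, so RNFL, MTR and macular volume cannot be placed on either side of 0.05. In Table 5 it is 1.04 to 1.38 times the one used, always in the direction of too many false positives: about 6 to 9% with six split patients and up to about 17 or 18% with none. The DTI fractional anisotropy and radial diffusivity differences survive every case examined.

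That eyes were counted as independent rests on reproducing the printed values. The sizes rest on an assumed correlation of 0.3 to 0.9, taken as equal in patients and controls, and on the four possible pairings. Nothing is concluded about the efficacy analysis.

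**What to change.** Reanalyse every eye-level outcome in Tables 4 and 5 with a linear mixed model that has a random participant effect and small-sample degrees of freedom based on the number of people. An equivalent person-level or paired analysis would also do. Report how many patients have one eye affected, both or neither, so that a reader can see how much of Table 4 is a within-person contrast. State that the participant is the unit of inference for eye-level outcomes. As a precaution, state the same unit for the pre/post efficacy analysis before it is run.

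The cost is re-running the models on data already collected; no new measurements are needed. With 10 and 8 people some intervals will be wide, and the text on RNFL and the patient-control differences may need rewording.

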## Methods

### Trial design

The MSCIMS Trial uses an 18-month pre-test : post-test design with a single treatment of autologous mesenchymal stem cells at 12 months. A parallel cohort of normative controls was also recruited to determine inter-session variability of assessment methods.

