### Trial objectives

MSCIMS aims to establish the safety and feasibility of autologous intravenous mesenchymal stem cell therapy in multiple sclerosis (phase IIA). The primary objective is to describe the safety profile over six months of intravenously administered autologous MSCs at a dose of 1 - 2 × 10^6 ^cells / kg in patients with multiple sclerosis. The secondary objective is to explore the potential efficacy over six months of intravenously administered autologous MSCs at a dose of 1 - 2 × 10^6 ^cells / kg by clinical, neurophysiological and imaging assessments.

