### Intervention dose, route, and administration procedures

Participants received one treatment with autologous MSCs administered intravenously at a dose of 1 - 2 × 10^6 ^cells/kg. Administration was performed as a day-case procedure following pre-medication with chlorpheniramine 10 mg, hydrocortisone 100 mg, and metoclopramide 10 mg. Cryopreserved MSCs were thawed (≤ 4 minutes) and immediately infused over 15 minutes. Administration (mean 167.2 ml, range: 89 to 246 ml) was followed by infusion of normal saline (500 ml) over 4 hours. Participants were monitored clinically for evidence of adverse reactions over a minimum of 4 hours.

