### Outcome selection & assessment schedule

In order to increase power to detect efficacy through use of tailored outcomes, complementary eligibility criteria and outcome measures were selected allowing detailed assessment of participants with disease affecting the afferent visual pathway. Study of the entire visual pathway as a model of wider disease processes allows the use of clinical and paraclinical outcomes that can inform on aspects of both structure and function [13]. Participants were assessed at 12 (M-12) and 6 (M-6) months before treatment, immediately prior to treatment (M0), and at 3 (M3) and 6 (M6) months after treatment. Assessment at each time point was split into two visits with an interval of less than two weeks: clinical assessment and visual evoked potentials were performed in Cambridge, UK; MRI, optical coherence tomography (OCT), and neuro-ophthalmological assessments were performed in London, UK. In addition, patients were reviewed weekly on four occasions following treatment to assess immediate clinical response and monitor blood parameters including: full blood count, prothrombin time, accelerated partial thromboplastin time, erythrocyte sedimentation rate, serum urea & electrolytes, serum calcium and phosphate, serum albumin, bilirubin, alanine transaminase, aspartine transaminase. C-reactive protein, thyroid-stimulating hormone, complement C3 & C4, lymphocyte subsets, and serum IgG, IgA & IgM.

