### Clinical outcome measures

Detailed neurological and medical history was obtained at screening and updated at each visit. Specific enquiry for adverse events was performed and participants encouraged to keep written records of interim events. Clinical outcomes assessed at each visit were: Multiple Sclerosis Impact Scale -- 29 (MSIS-29), Beck's Depression Inventory II (BDI-II), Addenbrooke's Cognitive Examination - Revised (ACE-R), Multiple Sclerosis Functional Composite (MSFC), and EDSS. Neuro-opthalmological outcomes assessed at each visit were: Visual acuity using a retro-illuminated EDTRS chart, Contrast Acuity using retro-illuminated Sloan charts, Colour vision using the Farnsworth-Munsell 100-Hue test, and Visual Fields by automated static perimetry (Humphrey field analyser, 30-2 protocol).

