In order to establish the safety profile of the intervention, selection and timing of appropriate outcomes has been guided by the published literature on intravenous MSC therapy. Immediate adverse events consistent with type I hypersensitivity (pruritis, rash, fever) are reported in approximately 10% of subjects following intravenous administration of autologous or allogeneic MSCs. Intensive monitoring for evidence of allergic reactions is therefore scheduled around the time of infusion. Medium and long-term adverse event risks are less well characterised from the published literature, but include a theoretical risk of increased susceptibility to infection and neoplasia. Weekly assessment (×4) following infusion is designed to specifically screen for the former, and long term monitoring the latter. Given that the majority of the published cohort of patients who have undergone treatment with intravenous MSCs have been treated in the context of haematological malignancy, follow up of the MSCIMS trial cohort offers a unique opportunity to define long-term safety in a group with longer life-expectancy and a lower background rate of disease complications.

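### Adverse events are looked for far more often after treatment than before it, so the planned pre/post comparison can show an increase that is only better detection

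*Protocol article*

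**What the plan says.** - **Objective** (Trial objectives): "The primary objective is to describe the safety profile over six months of intravenously administered autologous MSCs".
- **Planned analysis** (Blinding and data analysis): "safety data will be analysed to assess whether the post-intervention period is associated with an increase in adverse events". No comparator window, scale or event class is given.
- **Design** (Trial design): an "18-month pre-test : post-test design with a single treatment of autologous mesenchymal stem cells at 12 months". The healthy controls are there to measure variability between sessions. They are not an adverse-event comparator.
- **Routine visits** (Outcome selection & assessment schedule): M-12, M-6 and M0 up to treatment, then M3 and M6.
- **Extra contacts after treatment only**: in the same section, "patients were reviewed weekly on four occasions following treatment to assess immediate clinical response and monitor blood parameters". Under Intervention dose, route, and administration procedures: "Participants were monitored clinically for evidence of adverse reactions over a minimum of 4 hours".
- **Purpose of the weekly reviews** (Discussion, where the former means infection): "Weekly assessment (×4) following infusion is designed to specifically screen for the former".
- **How events are collected** (Clinical outcome measures): "Specific enquiry for adverse events was performed and participants encouraged to keep written records of interim events".

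**The concern.** A before/after comparison of adverse events is interpretable only if events have a similar chance of being recorded in both periods. Here they do not. Mild or short-lived events in the pre-treatment year are found only if the participant wrote them down or remembers them at a visit up to 6 months later. The same event in the first month after treatment meets a review within a week. A laboratory abnormality can be found by the described panel only after treatment. Infection is affected most directly, because the weekly reviews were set up to look for it and no matching pre-treatment screen is described.

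Safety is the primary objective, the treated cohort is ten people, and the results are meant to inform later studies. A false signal, or false reassurance, would be carried forward.

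**Working it through.** The article gives no adverse-event rate, significance level or power for this comparison, so there is no figure to reproduce. The contact counts below come from the document. Everything after them rests on stated assumptions.

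**1. Contact density**
- Before: M-6 and M0, so 2/12 = 0.17 per patient-month (3/12 = 0.25 with M-12).
- After: 4 weekly reviews + M3 + M6, so 6/6 = 1.0 per patient-month, with infusion day not counted.
- Ratio: 1.0/0.167 = 6, or 1.0/0.25 = 4. With only M-6 to M0 as comparator it is (6/6)/(1/6) = 6.
- Blood panels described: 0 before, 4 after.

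**2. Capture-fraction model, equal true rates.** Assumed capture: c6 = 0.40 to 0.70 with 6-monthly enquiry, 0.90 in the month of weekly reviews, c3 = 0.60 to 0.80 with 3-monthly enquiry.

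Spurious rate ratio = [(0.9 × 1 + c3 × 5)/6] / c6

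- c6 = 0.7, c3 = 0.7: (4.4/6)/0.7 = 1.05
- c6 = 0.4, c3 = 0.8: (4.9/6)/0.4 = 2.04
- c6 = 0.7, c3 = 0.6: (3.9/6)/0.7 = 0.93

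The last case needs 3-monthly enquiry to capture less than 6-monthly enquiry, which is implausible. Requiring c3 to be at least c6 gives 1.05 to 2.04.

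**3. Recall-loss model, equal true rates.** The detected fraction over look-back intervals L is the sum of (1 − exp(−kL))/k divided by the sum of L, with k = ln 2/half-life. Intervals in months are 6 and 6 before; 4 × 0.23, 2.08 and 3 after. The false-increase column assumes 60 detected events in total, 12 months before against 6 after, and a one-sided exact conditional binomial test at 0.025 with null post-treatment share 6/18 (actual size 2.2%).

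| Recall half-life (months) | Detected before | Detected after | Spurious rate ratio | Chance of a false increase | Rate ratio without weekly-only events |
|---|---|---|---|---|---|
| 1 | 0.237 | 0.536 | 2.26 | 87% | 1.78 |
| 3 | 0.541 | 0.785 | 1.45 | 28% | 1.33 |
| 6 | 0.721 | 0.882 | 1.22 | 10.5% | 1.17 |
| 12 | 0.845 | 0.938 | 1.11 | 5.2% | 1.09 |

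Both pre-treatment intervals are 6 months, so these rate ratios are the same whether the comparator is the full 12 months or only M-6 to M0.

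**4. Dependence on scale.** If raw counts over 12 and 6 months were compared, equal rates and equal capture would give 6/12 = 0.5. With the recall losses above, the count ratio is 1.13, 0.73, 0.61 and 0.56. On that scale the longer pre-period would mostly hide an increase.

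**The case against.** **The sentence states a purpose, not a specified test.** This stands. A reader might infer that the article sets six months after treatment against the whole preceding year, perhaps as raw counts. It does not say so. Because the objective covers six months, M-6 to M0 is an equally open comparator. The raw-count result in step 4 therefore shows why the scale matters; it is not a criticism of a chosen analysis.

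**It is not called the primary comparison.** This also stands. The primary objective is worded as description, and the analysis sentence carries no such label. It is, however, the only safety analysis the article states, and it goes beyond description.

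**Windows, rates and event classes belong in an analysis plan that is not shown.** This is right as far as their absence goes, and their absence is not the point here. The point is that the stated comparison conflicts with the stated schedule. No analysis plan can create weekly reviews or blood panels before treatment.

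**Pre-treatment contact is undercounted.** Serology, clotting tests and bone marrow aspiration also preceded treatment, and events from aspiration could raise the pre-treatment rate. The article does not describe adverse-event enquiry at those contacts, so they are not counted, but they could offset part of the bias. Written records in both periods also help with symptoms. They were encouraged rather than required, and they do not reveal laboratory abnormalities.

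**The error is in the cautious direction.** On a rate scale it points to harm, and no decision rule depends on it. That lowers the stakes, but a spurious signal still misinforms later trials.

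**Conclusion.** The concern holds. Ascertainment after treatment is four to six times as dense per month as before it, and the planned assessment of an increase runs across that divide. On a rate scale, with no true effect, the apparent ratio is about 1.05 to 2.04 under the capture assumptions (with 3-monthly capture at least as good as 6-monthly), or 1.11 to 2.26 for recall half-lives from 12 months down to 1. The direction on that scale is the firm part. The size is not: if recall is good and records are well kept, the distortion is small.

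A reader might go further and conclude that the trial's primary test is invalid, or that a false increase is to be expected. The article supports neither. It names no primary test, window or scale, and the chance of a false increase depends strongly on the assumed recall and event total.

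**What to change.** In Blinding and data analysis:

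1. Make the pre/post comparison on events per person-month, and name the pre-treatment window.
2. Base it on the events least dependent on visit frequency: serious events, relapses, and events from participant records or from enquiry at the M-visits.
3. Report infusion-day events, events found only at the weekly reviews, and laboratory abnormalities descriptively with exact confidence limits, outside the comparison.
4. State as a limitation that look-back at the M-visits remains 6 months before and 3 months after treatment, so an increase, or its absence, cannot be attributed to the cells alone.

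This reduces the bias without removing it. In the recall model, dropping weekly-only events takes the ratio from 1.45 to 1.33 at a 3-month half-life, and from 2.26 to 1.78 at 1 month. Giving weight to serious events and relapses should reduce it further.

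The cost is analysis wording only; the visit schedule does not change. The downside is that fewer events enter the comparison. Those left out include infections found only at the weekly reviews, which are the events those reviews were meant to find. All of them are still reported.
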